### Assessment of Adverse Event Severity

Adverse events will be categorized using the Medical Dictionary for Regulatory Activities (MedDRA) classification system. Investigators must grade each adverse event according to its severity based on the CTCAE version 5.0. If the severity of an individual adverse event is not graded in the text, the investigator may use their medical judgment to assign a grade based on the levels defined by CTCAE (ranging from Grade 1 to Grade 5).

Table 10 NCI-CTCAE Adverse Event Grading

| Grading | Description |
| --- | --- |
| Grade 1 | Mild; asymptomatic or mild symptoms; clinical or diagnostic observations only; intervention not indicated. |
| Grade 2 | Moderate; minimal, local, or non-invasive intervention indicated; age-related instrumental activities of daily living are limited. |
| Grade 3 | Severe or medically significant but not immediately life-threatening; hospitalization or prolongation of existing hospitalization indicated; disabling; limitations in activities of daily living. |
| Grade 4 | Life-threatening; urgent intervention indicated. |
| Grade 5 | Death |

Note: *Instrumental Activities of Daily Living (IADLs) refer to tasks such as cooking, shopping for groceries or clothing, using the telephone, managing finances, etc.
**Activities of Daily Living (ADLs) refer to tasks such as bathing, dressing and undressing, eating, toileting, and taking medications, as opposed to being bedridden.

### Assessment of the Relationship Between Adverse Events and Investigational Drug

The investigator should conduct a comprehensive analysis of the specific circumstances surrounding the adverse events experienced by the subjects, taking into account the subjects' medical history, concomitant conditions, and concomitant medications, in order to assess the relationship between the adverse events and the drug. The investigator should perform a causal analysis of the symptoms presented by the subjects during the medication process to evaluate any potential associations between the adverse events and the investigational drug. The considerations for causal analysis include the following five aspects:

1. Is there a reasonable temporal relationship between the start of medication and the occurrence of the adverse event (AE)?
2. Does the AE correspond to known types of AEs associated with the drug (as per literature)?
3. Can the AE be explained by concomitant medications, previous medications, the patient's clinical condition, or the effects of other therapies (alternative explanations)?
4. Does the AE resolve or lessen after discontinuation or dose reduction of the medication (resolution after discontinuation)?
5. Does the AE reoccur upon re-exposure to the same drug (recurrence upon re-administration)?

Assessment of Adverse Events and Causal Relationship with the Drug: Based on the five criteria mentioned above, the causal relationship will be analyzed and classified into five levels: definitely related, probably related, possibly related, probably not related, and definitely not related (Table 10).

Table 11 Relevant Criteria for Assessing Adverse Events

| Considerations | Drug Administration Occurred | Consistent with Literature | Other Explanations | Disappearance Upon Discontinuation | Reappearance Upon Readministration |
| --- | --- | --- | --- | --- | --- |
| Definitely Related | + | + | - | + | + |
| Likely Related | + | + | - | + | ？ |
| Possibly Related | + | + | ± | ± | ？ |
| Possibly Unrelated | + | - | ± | ± | ？ |
| Definitely Unrelated | - | - | + | - | - |
| **Note:** “+” indicates affirmative; “-” indicates negative; “±” indicates uncertain; “?” indicates unknown. | | | | | |

### Recording, Management, and Follow-Up of Adverse Events

The investigator should carefully observe any adverse events that occur in subjects during the clinical study and ask subjects to honestly report any changes in their condition after taking the medication, avoiding leading questions. While observing efficacy, the investigator should also pay attention to adverse events or unexpected side effects (including symptoms, signs, and laboratory findings). All adverse events, regardless of whether they are related to the investigational drug, should be documented in detail in the eCRF, including the time of onset, symptoms, signs, severity, duration, laboratory test results, treatment methods, course of events, outcomes, and follow-up times. Information about concomitant medications should also be recorded in detail to facilitate analysis of the relationship between the adverse events and the investigational drug. Documentation should be signed and dated.

When an adverse event is identified during the trial, the investigator may take necessary actions based on the clinical situation, such as adjusting the dose or temporarily interrupting the medication, and decide whether to terminate the trial. In the case of a serious adverse event, the sponsoring institution must immediately take necessary actions to ensure the safety of the subjects.

All adverse events should be tracked until they return to normal or baseline levels to ensure the safety of the subjects. If an adverse event or its sequelae persist, follow-up should continue until the results are normal or the clinical manifestations stabilize. The follow-up method may vary based on the severity of the adverse event and can include hospitalization, outpatient visits, home visits, phone calls, or correspondence.

**Adverse events should be recorded starting from the time the subject signs the informed consent form.**

## Serious Adverse Events

Serious Adverse Event Handling Process

[figure not shown]

According to the requirements of the 2020 version of GCP, the handling process for SAEs is illustrated in the diagram.

Except for serious adverse events that do not require immediate reporting as specified in the study protocol or other documents (such as the investigator's brochure), the investigator must submit a written report of all SAEs to the sponsor within 24 hours of the event's occurrence or upon becoming aware of the event. For reports involving death, the investigator should provide the sponsor and the ethics committee with any additional necessary information, such as autopsy reports and final medical reports.

Upon receiving any safety-related information from any source, the sponsor must promptly analyze and assess it, including its severity, relevance to the investigational drug, and whether it is an anticipated event. The sponsor should report any suspected unexpected serious adverse reactions (SUSARs) to all investigators participating in the clinical trial, as well as to the regulatory authorities and health departments.

Investigators who receive safety information related to the clinical trial from the sponsor should promptly acknowledge receipt and read it. They should consider whether to make any necessary adjustments to the treatment of the subjects and communicate with the subjects as soon as possible if necessary. Additionally, they should report the SUSARs provided by the sponsor to the ethics committee.

Handling Measures: In the event of an emergency involving a patient, the investigator at the trial site should take appropriate actions based on the medication and the symptoms presented, and notify the clinical monitor of the handling results. The investigator should document the cause, date, actions taken, outcomes, and sign the SAE report form in detail.

Follow-up on Unresolved Adverse Events: All adverse events should be tracked until they are adequately resolved or the condition stabilizes.

## Anticipated/Unexpected Adverse Events

### Anticipated Adverse Event

Based on the preclinical safety data of this drug and clinical experience with similar HDAC inhibitors, the anticipated adverse events may include:

1. Gastrointestinal abnormalities: nausea, vomiting, diarrhea, bloating, decreased appetite
2. Blood and lymphatic system abnormalities: thrombocytopenia, neutropenia, lymphopenia
3. Cardiac abnormalities: prolonged QTc interval, tachycardia, arrhythmia
4. Hepatobiliary abnormalities: elevated ALT, AST, ALP, TBIL
5. Respiratory abnormalities: dyspnea, pulmonary edema
6. Metabolic abnormalities: hyperglycemia, hyperuricemia, hypophosphatemia, hyponatremia, hypokalemia
7. Psychiatric abnormalities: insomnia
8. Neurological abnormalities: headache, dizziness
9. Vascular abnormalities: hypotension
10. Renal function abnormalities: elevated SCr
11. Infections, pneumonia
12. Fatigue, weakness, fever
13. Weight loss
14. Hemorrhage

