#### Chronic toxicity test in non-rodent Beagle dogs administered intravenously.

In this study, the low, medium, and high dose groups were set at 0.3, 1, and 3 mg/kg, respectively. The excipient was set at a high dose of 45 mg/kg. In the low dose group, occasional vomiting was observed; in the medium dose group, symptoms included vomiting, loose stools, and dark red stools; in the high dose group, symptoms included vomiting and dark red stools. Four dogs (4/10, 2 females and 2 males) died between days 13 and 26 of the experiment. Electrocardiogram (ECG) analysis showed that in the high dose group, male dogs exhibited increased heart rates and a slight prolongation of QTc (9.6%). Hematological analysis revealed that PLT, RET, and RET% were partially or fully reduced in the low, medium, and high dose groups, with an increase in APTT, indicating a dose-dependent relationship. Biochemical analysis showed that TP, TG, ALP, HDL, K+, and other parameters were partially or fully reduced in all dosing groups, also demonstrating a dose-dependent relationship. The primary toxic target organs or systems included the immune system (spleen, thymus, lymph nodes), digestive system (esophagus, liver, pancreas, intestine), kidneys, heart, lungs, trachea, testes, bone marrow, and injection site. There was a dose-dependent relationship, and recovery was observed during the recovery period. The highest no serious toxicity dose (HNSTD) was determined to be 1 mg/kg.

In conclusion, in the chronic toxicity study of injectable Purinostat Mesylate in dogs, the no observed adverse effect level (NOAEL) was found to be below 0.3 mg/kg, while the highest no serious toxicity dose (HNSTD) was 1 mg/kg.

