## Definition of DLT

Any drug-related toxicity occurring within 25 days after the first dose of the investigational drug, as defined by CTCAE version 5.0, that is considered related to the investigational drug (including definitely related, probably related, or possibly related) will be regarded as a DLT:

1. Hematologic Toxicity

- Grade 3 febrile neutropenia, defined as an absolute neutrophil count (ANC) < 1.0 × 10^9^/L accompanied by fever, with a temperature > 38.3℃, or a temperature sustained ≥ 38.0℃ for more than 1 hour;
- Grade 4 neutropenia without fever lasting ≥ 5 days;
- Grade 3 thrombocytopenia (25×10^9^/L < platelet count≤50×10^9^/L) accompanied by bleeding of Grade 2 or higher according to the WHO bleeding classification (2017 revised version), or Grade 4 thrombocytopenia lasting≥7 days with platelet transfusion treatment occurring≥2 times (excluding acute leukemia patients).

1. Any Grade 3 or higher non-hematologic toxicity, including but not limited to:

- Grade 3 or higher QT interval prolongation;
- Hepatic toxicity: If the baseline levels of ALT, AST, or TBIL for the subject are ≤ Grade 1, then drug-related Grade 3 toxicity will be considered as DLT.

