**The following situations are excluded:**

- Grade 3 fatigue, weakness, or fever;
- Grade 4 infusion reactions;
- Grade 3 controllable hypertension (systolic blood pressure ≥ 160 mmHg or diastolic blood pressure≥100 mmHg);
- Grade 3 nausea or vomiting lasting less than 72 hours, with adequate antiemetic and supportive treatment provided;
- Grade 3 diarrhea lasting less than 72 hours, with adequate antidiarrheal and supportive treatment provided;
- Grade 3 or 4 electrolyte abnormalities that can improve to Grade 2 or lower within 72 hours;
- Hair loss.

1. Patients with Acute Leukemia

- Persistent pancytopenia lasting > 42 days, accompanied by bone marrow hypoplasia (bone marrow cellularity < 5%) and the absence of leukemic cells in peripheral blood and bone marrow, will be considered a dose-limiting toxicity (DLT) due to bone marrow suppression. Pancytopenia is defined as leukocyte count < 4.0 × 10^9^/L, hemoglobin < 100 g/L, and platelet count < 100 × 10^9^/L.
- If the investigator cannot attribute any of the following events to a clearly identifiable cause (such as tumor progression, underlying or concurrent diseases, or concomitant medications), these events will be considered dose-limiting toxicities: hematologic toxicities possibly related to the study drug, grade 3 or higher non-hematologic toxicities, with the following exceptions:
- Alopecia
- Grade 3 fatigue, weakness, anorexia, fever, or constipation
- Grade 3 nausea, vomiting, or diarrhea that does not require tube feeding, intravenous nutritional support (TPN), or hospitalization
- Infections, bleeding, or other expected direct complications caused by underlying active leukemia

1. Others: Significant medical events deemed by the investigator to be possibly related to the study drug and discussed with the sponsor may be considered dose-limiting toxicities (DLT).
2. Any grade 5 adverse events.
3. Participants who have not recovered from toxicity and have interrupted treatment for more than 14 days (excluding interruptions greater than 14 days due to hematologic toxicity in acute leukemia).

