## Screening Phase（D-14 ~ D0）

After the subject signs the informed consent form, the following items will be conducted within 2 weeks prior to the first administration (D-14 to D0):

- Signing the informed consent form
- Tissue or cellular pathology
- Demographic information (age, gender, height, weight, etc.)
- Medical history and treatment history
- Allergy history
- Review of inclusion and exclusion criteria
- ECOG performance status
- Vital signs: including temperature, heart rate, respiratory rate, and blood pressure (systolic and diastolic)
- Physical examination: including examinations of the skin, mucous membranes, lymph nodes, head, neck, chest, abdomen, spine/extremities, and nervous system
- Urine or blood pregnancy test
- Laboratory tests:
- Complete blood count: red blood cell count, hemoglobin, platelet count, white blood cell count, neutrophil count, lymphocyte count
- Urinalysis: urine protein, urine red blood cells, urine white blood cells
- Blood biochemistry: serum creatinine, urea, total bilirubin, alanine aminotransferase (ALT), aspartate aminotransferase (AST), alkaline phosphatase, total protein, albumin, electrolytes (K+, Na+, Ca2+, Mg2+, Cl-), total cholesterol, low-density lipoprotein (LDL), high-density lipoprotein (HDL), creatine kinase (CK), creatine kinase isoenzyme (CK-MB), α-hydroxybutyrate dehydrogenase (α-HBDH), lactate dehydrogenase, fasting blood glucose
- Coagulation function: prothrombin time (PT), activated partial thromboplastin time (APTT), thrombin time (TT), fibrinogen (FIB)
- M Protein Testing: Conducted only for patients with multiple myeloma, including: (1) serum protein electrophoresis (Albumin, Alpha 1, Alpha 2, Beta 1, Beta 2, Gamma, M-spike); (2) immunofixation electrophoresis (IgG, IgA, IgM, light chain types); (3) β2-microglobulin (β2-MG); (4) serum immunoglobulin quantification (serum IgG, serum IgA, serum IgM, serum kappa light chains, serum lambda light chains, kappa/lambda ratio).
- 12-Lead Electrocardiogram: PR interval, QRS duration, QT interval, QTc interval.
- Virology Testing: HIV testing (antibodies, antigens), HCV testing (antibodies), HBV testing (HBsAg, HBsAb, HBcAb, HBeAg, HBeAb, HBV DNA titer).

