## Multiple-Dose Administration Phase（D8-D25）

After the single-dose administration phase is completed, if the subject tolerates the treatment well, they will enter the multiple-dose administration phase.

- IV Infusion Administration on D8, D11, and D15
- PK Blood Sample Collection:

On D11: collect blood samples 0.5 hours before administration.

On D15: collect blood samples within 0.5 hours before administration, and at 5 minutes, 10 minutes, 20 minutes, 30 minutes (immediately after administration), 32 minutes, 35 minutes, 45 minutes, 1 hour, 2 hours, 4 hours, 8 hours, and 12 hours after administration (3 mL each time).

- Biomarker Blood Sample Collection (only for leukemia patients):

On D8: collect blood samples within 0.5 hours before administration, and at 1 hour, 4 hours, and 24 hours (D9) after administration (4 mL each time).

On D11: collect blood samples within 0.5 hours before administration and at 1 hour after administration (4 mL each time).

On D15: collect blood samples within 0.5 hours before administration, and at 1 hour, 4 hours, 24 hours (D16), 48 hours (D17), and 72 hours (D18) after administration (4 mL each time).

- Vital Signs: Including temperature, heart rate, respiratory rate, and blood pressure (systolic and diastolic), to be checked once within 0.5 hours before each administration and again 2 hours after administration on D8, D11, and D15, as well as once on D25.
- Physical Examination: Includes examination of the skin, mucous membranes, lymph nodes, head, neck, chest, abdomen, spine/extremities, and nervous system. This will be conducted once on D11, D15, and D25.
- Laboratory Tests: These will be conducted once on D11, D15, and D25.
- Complete Blood Count (CBC): Red blood cell count, hemoglobin, platelet count, white blood cell count, neutrophil count, lymphocyte count.
- Urinalysis: Urine protein, urine red blood cells, urine white blood cells.
- Blood Biochemistry: Blood creatinine, urea, total bilirubin, alanine transaminase (ALT), aspartate transaminase (AST), alkaline phosphatase, total protein, albumin, electrolytes (K+, Na+, Ca2+, Mg2+, Cl-), total cholesterol, low-density lipoprotein (LDL), high-density lipoprotein (HDL), creatine kinase (CK), creatine kinase isoenzyme (CK-MB), α-hydroxybutyrate dehydrogenase (α-HBDH), lactate dehydrogenase (LDH), fasting blood glucose.
- Coagulation Function: Prothrombin time (PT), activated partial thromboplastin time (APTT), thrombin time (TT), fibrinogen (FIB).

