## Criteria for Mild Abnormal Laboratory Values

**Criteria for Mild Abnormal Laboratory Values - NCI CTCAE v5.0 Grade 1**

| Laboratory Test Item | Mildly Abnormal Criteria | Laboratory Test Item | Mildly Abnormal Criteria |
| --- | --- | --- | --- |
| Hb | < LLN - 100 g/L | Cr | > ULN – 1.5×ULN |
| WBC | < LLN - 3000/mm^3^ | Na | > ULN – 150 mmol/L  < LLN – 130 mmol/L |
| N | < LLN - 1500/mm^3^ | K | > ULN – 5.5 mmol/L  < LLN – 3.0 mmol/L |
| L | < LLN - 800/mm^3^ | Ca | > ULN – 2.9 mmol/L  < LLN – 2.0 mmol/L |
| Plt | < LLN - 75000/mm^3^ | Mg | > ULN – 1.23 mmol/L  < LLN – 0.5 mmol/L |
| BIL | > ULN - 1.5×ULN | P | < LLN – 0.8 mmol/L |
| ALT | > ULN - 2.5×ULN | Glu | > ULN – 8.9 mmol/L  < LLN – 3.0 mmol/L |
| AST | > ULN - 2.5×ULN | TG | > ULN – 2.5×ULN |
| ALP | > ULN - 2.5×ULN | CHOL | > ULN – 7.75 mmol/L |
| CPK | > ULN - 2.5×ULN | CK-MB | > ULN |
| LDH | > ULN - 2.5×ULN | Troponin I | > ULN |
| α-HDBD | > ULN - 2.5×ULN | CRP | > ULN |

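### Hyperuricemia and hypophosphatemia are anticipated toxicities, but no scheduled laboratory panel measures uric acid or phosphate

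*Protocol*

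**What the plan says.** Section 8.3.1 draws its list of anticipated events from the preclinical safety data and from clinical experience with similar HDAC inhibitors. Its metabolic line reads "Metabolic abnormalities: hyperglycemia, hyperuricemia, hypophosphatemia, hyponatremia, hypokalemia".

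Section 3.4 treats as dose-limiting "Any Grade 3 or higher non-hematologic toxicity, including but not limited to" QT prolongation and hepatic toxicity, provided that the event is related to the drug and falls within 25 days of the first dose. Among the exceptions are "Grade 3 or 4 electrolyte abnormalities that can improve to Grade 2 or lower within 72 hours". The synopsis carries the same rule and the same exception.

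The screening panel in Section 6.1 begins "Blood biochemistry: serum creatinine, urea, total bilirubin, alanine aminotransferase (ALT), aspartate aminotransferase (AST), alkaline phosphatase, total protein, albumin" and goes on to "electrolytes (K+, Na+, Ca2+, Mg2+, Cl-), total cholesterol, low-density lipoprotein (LDL), high-density lipoprotein (HDL"), followed by CK, CK-MB, α-HBDH, lactate dehydrogenase and fasting glucose. The multiple-dose phase, which falls within the DLT window, has the same electrolytes: "electrolytes (K+, Na+, Ca2+, Mg2+, Cl-), total cholesterol, low-density lipoprotein (LDL"). Appendix 14.3 gives a Grade 1 limit for P of "< LLN – 0.8 mmol/L".

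**The concern.** Both events are laboratory findings in the first place. If the assay is not on the schedule, whether an event enters the data depends on whether someone had a reason to order it. Such testing is likely to follow symptoms or local habit and need not be the same in every dose group, so rates by dose would not be comparable. A zero in the adverse event table could mean that the event did not occur or that it was not looked for.

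This reaches the primary purpose because the DLT count drives escalation in small cohorts. Under Section 3.2.4, none of 3 leads to the next dose and 1 of 3 leads to expansion; 1 of 6 leads to the next dose and 2 of 6 leads to a step back. One unobserved qualifying event is enough to change the branch taken.

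**Working it through.** No sample size or power figure is involved. The check compares the anticipated events with the scheduled tests.

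**Step 1: named metabolic events against panel items.**

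| Event in Section 8.3.1 | Analyte needed | In the panel? |
| --- | --- | --- |
| Hyperglycemia | Glucose | Yes (fasting glucose) |
| Hyponatremia | Sodium | Yes |
| Hypokalemia | Potassium | Yes |
| Hypophosphatemia | Phosphate | No |
| Hyperuricemia | Uric acid | No |

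So 3 of 5 events have a scheduled analyte and 5 − 3 = 2 do not. Urea is in the panel, but it is a different analyte from uric acid.

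**Step 2: every place where the panel is listed.** The synopsis safety assessments, the flowchart note, Sections 6.1, 6.2, 6.3, 6.4 and 6.5, and Section 7.1 make eight listings. All contain the same analytes, and K, Na, Ca, Mg and Cl are the only electrolytes. Phosphate appears in 0 of 8 and uric acid in 0 of 8. The blood count, urinalysis, coagulation and M-protein panels do not supply them either. None of the eight listings has open-ended wording.

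**Step 3: scheduled biochemistry draws affected.** Up to the end of the DLT window the draws are screening, D2, D7, D11, D15 and D25, which is 6, or 5 after the first dose. Each extension cycle adds D1, D11 and D21, and there is one at the end of the study. Neither analyte is scheduled at any of them.

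**Step 4: route to a DLT.** Drug-related hyperuricemia or hypophosphatemia of Grade 3 or higher falls under the general non-hematologic rule in Section 3.4. The electrolyte exception concerns phosphate only, because uric acid is not an electrolyte. It removes events that improve to Grade 2 or lower within 72 hours, so a persistent Grade 3 or 4 phosphate abnormality still counts.

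**Step 5: what scheduled phosphate would and would not give.** The draws after the first dose are 7 − 2 = 5, 11 − 7 = 4, 15 − 11 = 4 and 25 − 15 = 10 days apart. Adding phosphate would therefore supply a baseline and a chance of detection. It would not by itself show recovery within 72 hours, which would need follow-up tests, as it already does for sodium and potassium.

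**The case against.** The strongest reply is that the panels set the scheduled tests and prohibit nothing further. Section 8.1.1 counts abnormal laboratory findings as adverse events, and Section 8.1.4 has all of them recorded with their laboratory results. This stands. A reader might infer that the two events cannot be detected, or cannot enter the DLT count. The documents do not support that: an unscheduled result would be recorded and, if it qualified, would count. What is missing is systematic measurement.

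A reader might also infer that, without a screening value, an abnormal result could not be called treatment-emergent. Item 3 of the definition in Section 8.1.1 includes abnormalities found after dosing even if they might have been present before. The missing baseline therefore weakens attribution, and the comparison with pre-treatment values in Section 10.4, but not the recording of the event.

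Three further arguments should not be relied on.

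- **Rapid cell kill.** In acute leukemia or Burkitt lymphoma this would point to high phosphate, whereas the named event is low phosphate. The protocol names neither hyperphosphatemia nor tumor lysis.
- **The phosphorus row in Appendix 14.3.** The same table has triglycerides, troponin I and CRP, none of which is scheduled, so it reads as a general reference table. It adds to the mismatch but does not show that phosphate was meant to be drawn.
- **Pancreatic enzymes.** The chronic dog study names the "digestive system (esophagus, liver, pancreas, intestine") among its target organs, which might suggest a similar gap. But Section 8.3.1 anticipates no pancreatic event. The acute dog study's LIPC is not defined in the protocol; it rose only at 50 mg/kg, where all animals died, alongside several other markers, and biochemistry was normal at 10 mg/kg.

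Finally, Section 8.3.1 says only that these events may occur, and the risk control plan in Section 8.4 has no metabolic section. That lowers the weight of the point but does not remove the mismatch.

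**Conclusion.** The point holds as an inconsistency between the anticipated-event list and the scheduled tests. Two of the five named metabolic toxicities have no scheduled measurement at any visit, and either can count as a DLT. The scheduled tests will not detect them, and low or zero rates by dose group could reflect absence of measurement.

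The documents give no expected incidence for either event, so the number of missed events cannot be estimated. The DLT link assumes that such an event would be drug-related and graded 3 or higher. The protocol does not reproduce the CTCAE grade definitions for these terms. The finding also assumes that the repeated panel is the full list actually drawn.

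This should be corrected because it touches DLT ascertainment and the remedy is cheap. It does not invalidate the escalation design, and it is no reason to alter the DLT definition: writing phosphate into the electrolyte exception could only exempt events, since the general rule already covers persistent ones.

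**What to change.** Reconcile the panel with Section 8.3.1. Add inorganic phosphate and uric acid to the blood biochemistry list in the synopsis, the flowchart note, Sections 6.1 to 6.5 and Section 7.1, at the draws already scheduled and including screening. Leave the DLT clauses as they are.

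The cost is two analytes on an existing biochemistry sample, with protocol and eCRF wording to match; no new visit or blood draw is needed. The downside is a minor laboratory expense and some additional low-grade laboratory adverse events.
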